## Methods/design

### Study design and setting

We will perform a multicenter cluster-randomised clinical trial in 22 hospitals in six European countries (Belgium, Denmark, Italy, the Netherlands, Slovenia and the United Kingdom). Per country pairs of comparable hospitals (academic/non-academic) will be randomised to provide either ‘care as usual’ supplemented with ACP or ‘care as usual’. Cluster-randomisation prevents healthcare providers from giving patients in the control group (‘care as usual’) more opportunity to discuss their preferences than usual due to their experience with providing the intervention in the intervention group (‘care as usual’ supplemented with ACP). The nature of the intervention makes blinding, for both healthcare professionals and patients and their relatives, impossible.

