### Power calculation, sample size and feasibility of recruitment

With at least 11 intervention and 11 control hospitals each recruiting 34 lung cancer patients and 34 colorectal cancer patients (of which 25 in each tumour type group are expected to remain in the study until at least month 2.5), this multicentre cluster-randomised clinical trial has an overall power of 90 % to identify a minimum difference between intervention and control groups of half a standard deviation on the emotional functioning scale of the QLQ-C30 scale, assuming an intra-class correlation (ICC) of 0.1. On country level, these numbers give a power of 50 % to show such a difference (assuming an ICC of 0.05).

The main outcomes are measured at 2.5 months post-inclusion. Although included patients have an average life expectancy of at least 3 months, we expect that a number of them will die within 2.5 months after inclusion. Based on Dutch colorectal and lung cancer survival statistics [23], we conservatively assume that this will be the case for 15 % of included patients. Furthermore, we anticipate that around 10 % of included patients may drop out of the study for other reasons, resulting in a total attrition rate of 25 %. Based on this attrition rate and an estimated willingness of patients to participate of 33 %, the total number of eligible patients per hospital per cancer type needs to be 101 in a 2-year period, which is feasible in the participating hospitals.

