### Analyses

Analyses of the primary and secondary endpoints will be performed following the intention-to-treat principle. Descriptive statistics will be used to summarize characteristics of countries, hospitals and patients. Patient characteristics (age, gender, socio-economic class, educational level) will be compared at baseline between the intervention and control group. A multilevel modelling approach will be used to examine differences in the endpoints between the intervention and control groups, taking account of clustering effects at both hospital and country-level. All statistical tests will be two-sided and considered significant if *p* < 0.05. Repeated-measures analyses of variance will be conducted to assess the development of endpoints over time.

Subgroup analysis will be conducted by means of formal interaction tests for intervention and those variables which are more likely to influence the effect of the intervention itself: gender, age class (<65, 65–74, 75+), educational status, and country.

Those conducting the data analysis will be blinded as to whether the patient was included in the intervention group or in the control group.

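### The unqualified 50% country-level power holds only for two hospitals per arm under a normal approximation, and 22 hospitals in within-country pairs cannot give all six countries that

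*Protocol article*

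**What the plan says.** The power section of the protocol article starts from this design: "With at least 11 intervention and 11 control hospitals". Recruitment is set at 34 per tumour type in every hospital, and 25 of each 34 are assumed to be still available at 2.5 months. For the whole trial it claims 90% power for half a standard deviation on the emotional functioning scale at an ICC of 0.1. It then adds: "On country level, these numbers give a power of" 50% for the same difference, at an ICC of 0.05. It gives neither the number of hospitals per country nor a formula.

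Study design and setting describes "22 hospitals in six European countries" and says: "Per country pairs of comparable hospitals (academic/non-academic) will be randomised".

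The Analyses section plans two-sided tests at 5% and a multilevel model "taking account of clustering effects at both hospital and country-level". Country is one of the subgroup variables to be examined by a formal interaction test. The Background lists effects by country, among other subgroups, as a secondary objective.

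**The concern.** The 50% is stated for the country level in general, as if it applied to each of the six countries. Two features of the design work against that.

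- Within a country there are very few hospitals. The between-hospital variance that drives the precision of the arm comparison is then poorly estimated, and a normal approximation flatters the power.
- The number of pairs does not divide into two per country.

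At stake is how country results are read. A null result in a country would look more informative than it is. In a country with one intervention and one control hospital, an apparent effect may be no more than a difference between those two hospitals.

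**Working it through.** **Inputs from the protocol**
- Difference d = 0.5 SD; two-sided alpha 0.05.
- Country-level ICC ρ = 0.05, taken as given. The overall ICC of 0.1 could include variation between countries, so a lower value within a country is not in itself an error.
- Patients per hospital: m = 34 + 34 = 68 recruited, 25 + 25 = 50 evaluable at 2.5 months.
- 22 hospitals, randomised in pairs within six countries.

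**Assumptions (not in the protocol)**
- k hospitals per arm in a country: 1, 2 and 3 examined.
- Degrees of freedom when hospital variance is pooled over the trial: 22 − 6 × 2 = 10 if each country has its own arm means; 22 − 6 − 1 = 15 if the variance comes from a model with six country means and one common arm effect.

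**Formula.** Expected test statistic: δ = d / √[(2/k)(ρ + (1 − ρ)/m)]. The normal approximation refers δ to 1.96. The small-sample version uses a noncentral t distribution, with 2k − 2 degrees of freedom for a stand-alone country test.

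**Step 1: reproduce the stated 50%**
- k = 2, m = 50: design effect 1 + 49 × 0.05 = 3.45; effective size per arm 100/3.45 = 29.0; δ = 0.5 × √(29.0/2) = 1.90; normal power 48%.
- k = 2, m = 68: normal power 51%.
- m = 50 with k = 1 gives 27%, and with k = 3 gives 64%.

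So the stated figure is a rounded normal-approximation result for two hospitals per arm.

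**Step 2: allow for estimating the hospital variance (m = 50, ρ = 0.05)**

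| Pairs in country | Normal | Stand-alone t | Pooled variance, 10 df |
|---|---|---|---|
| 1 | 27% | none (0 df) | 23% |
| 2 | 48% | 20% (2 df, critical value 4.30) | 41% |
| 3 | 64% | 43% (4 df) | 56% |

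A simulation of 200,000 trials for the two-pair stand-alone test also gave 20.4%. With 15 df the two-pair pooled figure is 43%. The pooled column is power for a country-specific effect taken from the multilevel model, not power for the interaction test.

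**Step 3: count the pairs.** 22/2 = 11 pairs. Two pairs in each of six countries would need 6 × 2 = 12. At least one country therefore has a single pair, and giving any country three pairs leaves fewer for the others. With one pair, the arm contrast is the contrast between two hospitals, so a stand-alone analysis cannot separate the two.

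**Step 4: check the overall figure.** At 11 v 11, m = 50 and ρ = 0.1, power is 93% by the normal formula and 90% by t on 20 df. The stated 90% holds.

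**The case against.** Several points on the other side are sound.

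- **The 50% is not an arithmetic slip.** The usual design-effect formula gives 48% to 51% for two hospitals per arm. The dispute is over using it with four clusters and stating it without limits. This stands.
- **No stand-alone country test is planned.** The Analyses section specifies a multilevel model and an interaction test. A reader might take 20% as the power of the planned analysis, but the document does not support that. With hospital variance pooled, a two-pair country has about 41% to 43%, not far from 50%, and a three-pair country would exceed it at about 56%. This stands and narrows the point.
- **A reader might infer that the two stated powers rest on different standards**, because 90% matches the t distribution on 20 df while 50% matches the normal approximation. This is not established. The planned total of 1,360 equals 20 × 68, and 10 v 10 hospitals give 90.2% by the normal formula, so one normal-approximation standard could produce both figures. No formula is given.
- **A figure of 50% already signals low power, and country is one of several subgroup factors in a secondary objective.** This is fair and limits the severity.
- **The phrase at least 11 per arm leaves room for more hospitals.** The design is nevertheless given as 22, and the power sentence refers to those numbers.

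None of this rescues the figure for a one-pair country, where even the most favourable formula gives 27%.

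**Conclusion.** The point holds in a limited form. An unqualified 50% at country level is not what 22 paired hospitals in six countries deliver. For a two-pair country it is optimistic: about 41% to 43% with pooled hospital variance, about 20% alone. For at least one country it is out of reach: 27% by the normal formula, about 23% pooled at 10 df, and no stand-alone test.

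The single-pair conclusion rests only on counting, given 22 hospitals and within-country pairs. The power figures rest on 50 evaluable patients per hospital, an ICC of 0.05, the assumed numbers of hospitals per arm and, for the pooled figures, the assumed degrees of freedom and a hospital variance common to all countries. It would go too far to say that no country effect can be estimated in a one-pair country: the pooled model gives an estimate, but only by borrowing that variance.

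Severity is moderate. Sample size, overall power and the primary analysis do not change.

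**What to change.** Replace the country-level sentence in the power section with power by number of pairs and type of analysis: two pairs, about 20% stand-alone and about 41% with pooled hospital variance; one pair, not testable alone and about 23% pooled. State the assumptions beside the figures: 0.5 SD, ICC 0.05, 50 evaluable patients per hospital, 10 df for the pooled variance. Give the number of hospital pairs in each country.

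In the Analyses section, add that country-specific estimates are descriptive and reported with confidence intervals. Heterogeneity is to be judged by the country-by-arm interaction already planned, with hospital random effects and small-sample degrees of freedom.

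The cost is a sentence or two in each section and a less favourable stated power. Recruitment and randomisation are untouched.

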### Analyses

Analyses of the primary and secondary endpoints will be performed following the intention-to-treat principle. Descriptive statistics will be used to summarize characteristics of countries, hospitals and patients. Patient characteristics (age, gender, socio-economic class, educational level) will be compared at baseline between the intervention and control group. A multilevel modelling approach will be used to examine differences in the endpoints between the intervention and control groups, taking account of clustering effects at both hospital and country-level. All statistical tests will be two-sided and considered significant if *p* < 0.05. Repeated-measures analyses of variance will be conducted to assess the development of endpoints over time.

Subgroup analysis will be conducted by means of formal interaction tests for intervention and those variables which are more likely to influence the effect of the intervention itself: gender, age class (<65, 65–74, 75+), educational status, and country.

Those conducting the data analysis will be blinded as to whether the patient was included in the intervention group or in the control group.

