Questionnaire study. Patients will be asked to complete a written questionnaire about quality of life, symptoms, the decision-making process, patient activation, coping, and satisfaction with care (and the intervention) at baseline (i.e., the moment of inclusion, before the ACP program is delivered in the intervention group), and at 2.5 and 4.5 months after inclusion. If a patient dies during follow up (i.e., within one year after inclusion), a relative identified by the patient as next of kin will receive a questionnaire to assess the patient’s quality of end-of-life care and the relative’s own wellbeing.Medical file study. Data on patients’ survival will be collected, as well as preferences as documented and care as received to assess whether patients’ preferred care was congruent with received care. Data on care as received will also be used in the cost-effectiveness analysis. These medical files will be studied one year post-inclusion with a checklist.Study of recorded ACP sessions. Data will be obtained from audio recorded facilitated interview sessions. Compliance with the intervention will be systematically evaluated with a predefined checklist.

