In ACTION, we expect to encounter some challenges and possible limitations. First, patients may decline participation for different reasons. They may feel overwhelmed by the topics raised in the ACP intervention sessions and may not (yet) feel prepared to talk about these issues. We will use a patient-centered approach to facilitate study participation. Patients will receive information about the project through their treating specialist. Since patients may refuse because they do not want to engage in ACP conversations, non-response bias cannot be ruled out. Also selection bias cannot be ruled out, e.g. in intervention hospitals’ where including physicians may be more likely to ask patients who they think are more ‘open’ to ACP to participate in the study. If such ‘gatekeeping’ comes into play, the effect of the intervention may be overestimated. However, our approach to systematically assess all lung and colorectal cancer patients for eligibility, and subsequently invite all who are eligible to participate in the study may reduce this risk. Attrition is another potential limitation to this project. Attrition may occur because the condition of the patient might worsen such that further participation becomes impossible, or patients might die during follow-up. We try to limit attrition by adding the inclusion criterion of a minimal anticipated life-expectancy of three months and to measure our main outcome measure at 2.5 months. Third, the international character of this project might be a challenge, as a balance needs to be found between on the one hand testing a uniform intervention in the six countries, that on the other hand is tailored to the specific cultural, ethical and legal context of each country. Fourth, the extent to which actual care will be reflected in medical files can be questioned. Potentially, not all treatments that patients receive will be documented in the hospital medical files.

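### The stated comparison names hospital and country clustering but not the baseline emotional functioning score or the hospital type used to pair hospitals; both should be prespecified as model terms

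*Protocol article*

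**What the plan says.** - **Model (Analyses).** Endpoints are compared between arms by a multilevel approach "taking account of clustering effects at both hospital and country-level". No fixed covariate is named and none is ruled out. The same section lists four patient characteristics to be compared between arms at baseline (age, gender, socio-economic class, education). It also plans repeated-measures analyses of variance for change over time, and says "All statistical tests will be two-sided and considered significant if *p* < 0.05".
- **Randomisation (Study design and setting).** "Per country pairs of comparable hospitals (academic/non-academic) will be randomised" to ACP plus usual care or to usual care alone. Blinding of professionals, patients and relatives is described as impossible.
- **Baseline measurement (Measurements).** The questionnaire, which includes quality of life, is completed at inclusion, "before the ACP program is delivered in the intervention group", and again at 2.5 and 4.5 months.
- **Recruitment (Study procedures; Discussion).** Consent information is to be kept as alike as possible, but control patients are told little or nothing about the programme. The Discussion accepts that physicians in intervention hospitals may favour patients they see as open to ACP, and that in that case "the effect of the intervention may be overestimated". The mitigation offered is systematic eligibility assessment and invitation of everyone eligible.

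**The concern.** Two pieces of information that the design creates have no stated place in the comparison. The baseline emotional functioning score is the same scale as the outcome, taken before the intervention, and so is likely to be a strong predictor. Hospital type defines which hospitals count as comparable when pairs are formed; country, the outer level of the pairing, is already in the model, but type is not.

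This matters more here than in an individually randomised trial. Only 22 units are randomised, so chance imbalance between arms is plausible. Patients enter after their hospital's allocation is known, so randomisation does not protect against differential recruitment. If patients in the intervention arm start with better emotional functioning, part of that difference carries through to 2.5 months in an unadjusted contrast, in the direction the Discussion fears.

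A planned baseline comparison with no stated rule for acting on it also leaves room to choose covariates after imbalances have been seen.

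**Working it through.** **Inputs from the documents (power calculation section).** There are k = 11 hospitals per arm. For the number of evaluable patients, the article gives recruitment per hospital by tumour type, "of which 25 in each tumour type group are expected to remain in the study until at least month 2.5", so m = 25 + 25 = 50 per hospital. The difference sought is 0.5 SD, the ICC is 0.1, the test is two-sided at 0.05, and the stated power is 90%.

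**Inputs assumed, because the documents give none.** Baseline-to-follow-up correlation of 0.3 to 0.7 within hospitals (r_w) and 0 to 0.7 between hospitals (r_b); share f of between-hospital variance explained by hospital type, 0 to 0.5; baseline imbalance of 0.2 SD.

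**Step 1: the plan's own figure.** With total SD = 1, the between-hospital variance is V_b = 0.1 and the within-hospital variance is V_w = 0.9.

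SE = sqrt(2 × (V_b + V_w/m)/k) = sqrt(2 × (0.1 + 0.018)/11) = 0.1465 SD

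The noncentrality is 0.5/0.1465 = 3.414. The noncentral t with 2 × 11 − 2 = 20 df gives 90.1% power, so the stated 90% reproduces with no covariate.

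**Step 2: add the baseline score.** V_b becomes 0.1(1 − r_b²) and V_w becomes 0.9(1 − r_w²), with 19 df.

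| r_w | r_b | SE (SD) | Power |
|---|---|---|---|
| 0.3 | 0 | 0.1455 | 90.3% |
| 0.5 | 0 | 0.1437 | 91.0% |
| 0.3 | 0.3 | 0.1397 | 92.4% |
| 0.5 | 0.5 | 0.1268 | 96.2% |
| 0.7 | 0.7 | 0.1046 | 99.5% |

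Most of the gain comes from the between-hospital correlation: unadjusted, V_b contributes 0.1 of the 0.118 in the SE formula and patient-level variance only 0.018.

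**Step 3: add hospital type, or a larger set of strata, without the baseline score.** V_b becomes 0.1(1 − f).

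| f | Type only (19 df) | Country and type fixed (about 14 df) | Full pair effects (10 df) |
|---|---|---|---|
| 0 | 89.9% | 88.7% | 86.7% |
| 0.25 | 95.4% | 94.6% | 93.3% |
| 0.5 | 98.9% | 98.7% | 98.1% |

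If it explains nothing, hospital type costs about 0.2 points (90.1% to 89.9%) for one degree of freedom. Larger sets of strata cost more.

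**Step 4: both terms at the pessimistic end.** With r_w = 0.3, r_b = 0, f = 0 and 18 df, the SE stays at 0.1455, the noncentrality is 0.5/0.1455 = 3.437, and power is 90.1%, the same as unadjusted.

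**Step 5: bias from imbalance.** A baseline difference D between arms shifts the unadjusted contrast by about r × D. For D = 0.2 SD the shift is 0.3 × 0.2 = 0.06, 0.5 × 0.2 = 0.10 or 0.7 × 0.2 = 0.14 SD. Relative to the 0.5 SD target, that is 12%, 20% or 28%.

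**The case against.** The strongest objection is that this is silence in a condensed article. The Analyses section gives an approach, not a full model, and covariate lists and degrees-of-freedom methods commonly sit in the SAP, which is not shown. A reader might infer that the model contains clustering terms and nothing else; the text does not say so. Nor does baseline go unused, since repeated-measures analyses over time are also planned. This stands: omission is not exclusion, and if the SAP already names these terms the point is closed.

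A reader might also infer three stronger things that the documents do not support.

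- **That leaving out the pairing necessarily loses precision.** It need not. If the strata explain nothing, adding them lowers power (step 3), and ignoring the pairing tends to be conservative.
- **That adjustment is free.** One or two terms are nearly so, but a full set of country and type strata uses about 6 of the 20 df and can lower power to about 89%.
- **That the acknowledged recruitment bias goes uncorrected and that adjustment would correct it.** The article offers mitigation by systematic screening and by consent information kept as alike as possible. The feared selection is on openness to ACP, which neither baseline emotional functioning nor hospital type measures.

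What survives is that these two variables follow directly from the design, the article names neither in the comparison, and the mitigation it offers acts at recruitment rather than in the analysis.

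**Conclusion.** The point holds as a recommendation to specify the primary model more fully. It does not show that a stated figure is wrong: the 90% power stands without adjustment.

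The expected gain ranges from negligible to large. The baseline score alone takes power from 90.1% to between 90.3% and 99.5%, and hospital type alone to between 89.9% and 98.9%. These ranges rest wholly on the assumed correlations and variance shares. The downside of the two terms together is essentially nil over the range examined.

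The bias argument does not need a power gain: baseline adjustment takes out imbalance in measured emotional functioning, worth about 0.06 to 0.14 SD for an assumed 0.2 SD imbalance. It leaves selection on openness to ACP where it was.

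**What to change.** State the primary model in the protocol or SAP before any unblinded analysis:

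- Outcome: emotional functioning at 2.5 months.
- Fixed terms: arm, baseline emotional functioning, and hospital type (academic or non-academic).
- Keep the hospital and country terms already planned. Making country a fixed rather than a clustering term is optional, given its cost in degrees of freedom.
- Use a small-sample degrees-of-freedom method such as Satterthwaite or Kenward-Roger.
- Report the model without covariates as a sensitivity analysis.
- Say in the limitations that adjustment does not deal with selection on openness to ACP.

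The cost is wording only. Both variables are already collected, the two terms use about two degrees of freedom, and the sample size does not change. If the SAP already specifies this, a sentence confirming it is enough.

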### Qualitative study

A complementary qualitative study will be carried out in at least 3 of the 6 countries, to qualitatively explore the lived experience of engagement with the Respecting Choices intervention from the perspectives of patients, their Personal Representatives, healthcare providers and Respecting Choices facilitators. The patient and Personal Representative will undertake a facilitated advance care planning (ACP) conversation following the Respecting Choices program. Within two weeks of completing the ACP program they will be invited to take part in a baseline qualitative interview about their experiences. A follow up interview will occur 10–14 weeks after the initial intervention. At this second interview the patient will be asked whether he or she has discussed the Respecting Choices intervention with anyone from the healthcare team and for consent to contact this person. If the patient dies before the second interview, the Personal Representative will be contacted and invited for a qualitative interview. This will not be arranged until a minimum of six weeks after the patient’s death. Healthcare professionals identified by the patient as being closely involved in the care will be invited to participate in a single face to face, Skype or telephone interview. Respecting Choices facilitators will be invited to participate in a single focus group discussion. In each of the participating countries, the qualitative study will involve between 6–10 cases including a patient and where appropriate a Personal Representative and healthcare professionals. All interviews and focus groups will be recorded and transcribed verbatim. Data will be thematically analysed using a pre-defined coding framework which will be developed through an iterative process of discussion and consensus among the research team.

